### Sample size {14}

Based on a previous Cochrane review with meta-analysis [7], it is assumed that preoperative smoking cessation decreases the binary outcome of postoperative complications (yes or no) with a relative risk of 0.42. The mean postoperative CCI as a continuous measure in a retrospective chart review in a cohort without smoking cessation at the hospital of Lucerne was 13 and we therefore assume a CCI of 5.5 in the intervention group. The assumed standard deviation for the sample size calculation was 20. With anticipated 80% power, a two-sided significance level α of 5%, a sample size of 226 patients is planned. With an additional 10% dropout, our aim is to enrol 251 patients.

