## Assignment of interventions: allocation

### Sequence generation {16a}

Patients will be randomised in a 1:1 ratio to either the intervention or control group using the service of the University of Graz (www.randomizer.at). Before randomisation patients will be pre-stratified for age (≤60, >60 years) and procedure (intermediate versus high-risk procedures). Both factors have been identified in a previous retrospective cohort study at our institution as risk factors for complications. Minimization, as an efficient way to control for confounding in small to moderately sized trials, will be used. Also, minimization automatically ensures the concealment of random allocation since there is no pre-existing randomization list.

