## Statistical methods

### Statistical methods for primary and secondary outcomes {20a}

A detailed statistical analysis plan has been written up as an Additional file 3 to the submission. According to the intention to treat (ITT) principle, patients will be analysed according to the treatment group they have been assigned to by randomisation. The full analysis set (FAS) consists of the patients randomized and receiving surgery within 4 months after randomization. The FAS will be the primary population for the efficacy analysis.

Primary outcome CCI will be addressed with a multiple linear model, including a randomized treatment group, and the minimization variables (age ≤60 or >60 and intermediate or high-risk surgery) as independent variables. If after normality check with a qq-plot the residual distribution is skewed a transformation of the CCI may become necessary. To evaluate the between-group difference in CCI of the smoking cessation intervention versus the control group, adjusted for the above-defined confounders, the estimated between-group difference with 95% confidence interval and corresponding p-value will be reported. For the secondary outcomes, linear, logistic, or Poisson regression models including the randomized treatment group as an independent variable, will be used to estimate the treatment effect between treatment groups. Normality will again be checked using qq-plot and, if necessary, appropriate transformations of the dependent variable will be made.

For the comparison of readmission rates between the treatment groups, the date of discharge from the hospital after surgery will be chosen as the starting observational time point and a Poisson model, considering readmissions collectively, will be fitted to estimate the incidence rates of readmission per treatment group within 90 days after discharge. The result will be reported as a rate ratio (RR) and the Poisson model will be corrected for overdispersion if necessary.

To estimate the hazard ratio for the first readmission, again with starting time point at discharge, a Cox-model will be used.

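### The secondary-outcome models name only treatment group although allocation is minimised on age group and procedure risk; adding both factors would recover some power at no cost

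*Protocol article*

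**What the plan says.** Under Sequence generation {16a} the protocol article states "Patients will be randomised in a 1:1 ratio to either the intervention or control group". It adds "Before randomisation patients will be pre-stratified for age (≤60, >60 years) and procedure (intermediate versus high-risk procedures", and names the method: "Minimization, as an efficient way to control for confounding in small to moderately sized trials, will be used". On the choice of factors it says: "Both factors have been identified in a previous retrospective cohort study at our institution as risk factors for complications".

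Under Statistical methods for primary and secondary outcomes {20a}, the primary CCI model is specified as "including a randomized treatment group, and the minimization variables (age ≤60 or >60 and intermediate or high-risk surgery) as independent variables". Shortly afterwards the same section turns to the other endpoints: "For the secondary outcomes, linear, logistic, or Poisson regression models including the randomized treatment group as an independent variable, will be used". The Poisson model for readmissions, the Cox model for first readmission and the mixed-effects models for Fagerström score, SF-36 and cigarettes per day name no adjustment for the minimisation factors. The NicAlert result is compared by a chi-square test, which cannot carry covariates. Nowhere does the article extend the primary model's adjustment to the secondary outcomes.

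**The concern.** Minimisation forces the arms to be alike on age group and procedure risk. The treatment estimate therefore varies less from trial to trial than under simple randomisation. A model without the two factors does not know this. It leaves their variance in the residual and reports a standard error for an allocation that was not used.

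The article itself calls both factors risk factors for complications. Length of stay, cost, readmission and unplanned intermediate or intensive care admission follow closely from complications, so the factors plausibly predict them too. For those endpoints confidence intervals would be wider than needed and tests conservative, in a trial whose sample size was set for the CCI alone.

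**Working it through.** **The plan's own figure.** Under Sample size {14}: "With anticipated 80% power, a two-sided significance level α of 5%, a sample size of 226 patients is planned". The means are 13 and 5.5 (difference 7.5) and the SD is 20. The normal formula gives 2 × (1.960 + 0.842)² × 20² / 7.5² = 111.6, so 112 per arm. The t-based calculation gives 112.6, so 113 per arm and 226 in total, with power 80.5%. Allowing for 10% dropout, 226 / 0.9 = 251.1. The stated 226 and 251 reproduce. They concern the CCI only and serve here to set N and a reference effect of 7.5 / 20 = 0.375 SD.

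**Linear outcomes, by formula.** Let the two factors explain a share R² of the variance σ² of an outcome. With the arms balanced on both factors:

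- true variance of the treatment difference: 4σ²(1 − R²) / N
- variance reported by the treatment-only model: 4σ² / N
- ratio of reported to true SE: k = 1 / √(1 − R²)
- type I error: 2Φ(−1.96k)
- power for an effect of 0.375 residual SD: the true SE is 2 / √226 = 0.1330 residual SD, so power is Φ(0.375 / 0.1330 − 1.96k) = Φ(2.819 − 1.96k). The adjusted model has k = 1.

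R² is not in the documents, so a range is assumed:

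| R² | k | Type I error, treatment only | Power, treatment only | Power, adjusted |
|---|---|---|---|---|
| 2% | 1.01 | 4.8% | 79.9% | 80.5% |
| 5% | 1.03 | 4.4% | 79.0% | 80.5% |
| 10% | 1.05 | 3.9% | 77.4% | 80.5% |
| 20% | 1.12 | 2.8% | 73.5% | 80.5% |

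**Simulation check.** N = 226, 1:1 minimisation on two binary factors, 3,000 runs per scenario. Assumed: each factor present in 50% of patients, and probability 0.9 of assigning the balancing arm. Monte Carlo error on a 5% rejection rate is about ±0.8 points.

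| Model | Assumed strength | Type I error, treatment only | Type I error, adjusted | Power, treatment only | Power, adjusted |
|---|---|---|---|---|---|
| Linear | R² 5% | 4.3% | 4.9% | 79% | 81% |
| Linear | R² 10% | 3.7% | 5.4% | 76% | 80% |
| Linear | R² 20% | 3.1% | 5.5% | 74% | 81% |
| Logistic | OR 1.5 per factor | 4.1% | 4.4% | 58.0% | 58.9% |
| Logistic | OR 2 per factor | 4.1% | 4.6% | 57.7% | 59.8% |
| Logistic | OR 3 per factor | 3.9% | 5.0% | 52.2% | 56.9% |
| Poisson | RR 1.5 per factor | 4.5% | 4.8% | 67.6% | 67.7% |
| Poisson | RR 2 per factor | 3.9% | 4.7% | 68.4% | 70.0% |
| Poisson | RR 3 per factor | 3.2% | 5.0% | 73.3% | 78.3% |

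The treatment effect in the power columns is 0.375 residual SD (linear), a conditional odds ratio of 0.50 (logistic) or a rate ratio of 0.50 (Poisson, corrected for overdispersion).

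**Is minimisation the cause?** At R² 20% without minimisation, the treatment-only model reported an SE of 0.1485 against an actual 0.1504, and type I error was 5.6%. With minimisation it reported 0.1488 against 0.1348. The conservatism comes from balancing on the factors and then not modelling them.

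**Odds ratios.** With 30% risk on control at the midpoint of the factors, a conditional odds ratio of 0.50 corresponds to a marginal one of 0.505, 0.515 or 0.536 when each factor has OR 1.5, 2 or 3. The Poisson rate ratio does not shift. Cox and mixed-effects models were not simulated.

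**The case against.** Four objections deserve weight.

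*The text does not say treatment only.* The secondary models are described as *including* the treatment group, and the article refers to a detailed analysis plan in Additional file 3, which is not shown. A reader might infer that the factors have definitely been dropped. The documents do not establish that. What stands is the contrast: the same word introduces the full covariate list of the primary model, and the secondary list, given shortly afterwards, is shorter. If the analysis plan does adjust, the article's sentence still needs to match it.

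*The strength of the factors is unknown.* This stands. At R² 2% a separate simulation of 4,000 runs found type I error 5.0% unadjusted against 5.3% adjusted, and power 79.4% against 80.0%: no material loss.

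*Not every secondary outcome is affected.* This stands too. Nothing in the documents says that age or procedure risk predicts quality of life, nicotine dependence, cigarettes per day or abstinence. In the mixed-effects models the time-by-treatment term is largely a within-patient contrast, from which a factor's constant contribution cancels.

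*Unadjusted odds and hazard ratios are not biased.* A reader might infer that they are wrongly pulled towards 1. They estimate the marginal effect, and the adjusted ones estimate the conditional effect. This is non-collapsibility, a difference in estimand. Nor is the unadjusted logistic SE larger than the adjusted one: at OR 3 per factor with no treatment effect it is 0.286 against 0.306. It is too large only against its own actual variability of 0.273.

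**Conclusion.** The point holds as a free improvement. As written, the article names treatment group alone for the secondary models after minimising on two factors that it calls prognostic for complications. For continuous outcomes that the factors predict, the standard error is about 3% to 12% too large, type I error about 4.4% to 2.8%, and the power loss about 1 to 7 points, over an assumed R² of 5% to 20%. The logistic and Poisson simulations point the same way, with power losses from almost nil up to about 5 points. These figures rest on assumed prognostic strength, 50% prevalence of each factor and a minimisation probability of 0.9, none of which the documents give.

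The error is on the safe side: false positives are not inflated. The primary analysis, already adjusted, and the sample size are untouched. A reader might also take the differing covariate sets as a contradiction within the protocol. They are not, because no passage promises the same adjustment for all outcomes.

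**What to change.** In Statistical methods for primary and secondary outcomes {20a}, and in the analysis plan if it does not already say so, add one sentence: *All secondary-outcome models (linear, logistic, Poisson, Cox and mixed-effects) include treatment group and both minimisation variables, as in the primary model.*

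Supplement the NicAlert chi-square test with a logistic model for cotinine-confirmed abstinence that has the same terms. State that the adjusted odds and hazard ratios are conditional effects.

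The cost is one sentence before database lock and two extra parameters per model. Both factors are entered for every patient at allocation (Implementation {16c}), so no new data and no more patients are needed. Fixing the covariates in advance also removes a later choice between adjusted and unadjusted results.

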### Intervention description {11a}

The study intervention consists of an interview by a Tobacco Treatment Specialist (TTS) 4 weeks before surgery with individual counselling and offered nicotine substitution. All TTS have > 15 years of experience and underwent a postgraduation course for counselling smoking cessation. The intervention meeting is based on the Chronic Care Model (CCM) [11, 12] to improve the quality of ambulatory care through six interrelated system changes [13]: self-management support, decision support, delivery system design, clinical information systems, health care organisation, and community resources. In line with the CCM, the intervention will include the following elements adapted from Haas et al. randomized clinical trial [14] and are described in the treatment plan. In brief, the intervention includes:Informative content about advantages of smoking cessation [15] using information leaflets along with decision supportScheduling service for a motivational interview by a TSS in the office to provide educational and motivational content, explain the magnitude and profile of nicotine dependence and implement a treatment plan [16]For participants willing to quit smoking a preoperative quit day will be scheduled after the first intervention meeting 2–3 weeks before surgery. Time of a preoperative quit day may vary between patients, since our smoking intervention focuses on as early quit attempts as possible. Therefore, there will be a variety in patients with one or more quit attempts, with or without success, and patients who quit smoking in the postoperative period, only.Patients will be encouraged by a TSS to use nicotine replacement with patches/gums/pills at their own discretion. For smokers of 20 cigarettes per day or more, a 4-week supply of 21mg/day, 2-week supply of 14 mg/day and a 2-week supply of 7 mg/days patches will be provided. Patients who smoke between 10 and 20 cigarettes per day will receive a 4-week supply of 14 mg/day and a 4-week supply of 7 mg/day. Smokers of <10 cigarettes per day will be supplied with a 4- to 8-week supply of 7-mg/day patches. Bupropion or Varenicillin will be provided on an individual basis (all costs are covered by the patient’s insurance).

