### Outcomes {12}

The primary endpoint is the (CCI®) [9] within 90 days of surgery. The CCI is calculated as the sum of all Clavien–Dindo complications [17] (Additional file 1) that are weighted for their severity (multiplication of the median preference values from patients and physicians). The final formula yields a continuous scale that ranks the cumulative burden from any combination of complications from 0 to 100 in a single patient. As a composite complication score, the CCI has the advantage of reflecting the overall burden of the postoperative course that affects the health of patients and their quality of life. In addition, the CCI is a powerful endpoint in trials, as it allows sample size up to nine times lower compared with traditional morbidity endpoints [18]. Complications will be assessed from medical health records by an advanced nurse practitioner supported by a surgical resident and consultant, all of whom were already trained in the Clavien–Dindo classification in a pilot study. Outpatient information of complications treated at other institutions will be included.

Secondary endpoints are length and costs of hospital stay, readmission rates for inpatient hospital stay, smoking abstinence or nicotine reduction, nicotine dependence, mental health, quality of life, unplanned postoperative intermediate care or intensive care unit admissions and cost and. Secondary endpoints will be recorded up to a 12-month postoperative follow-up period and will be compared between the intervention and control group. Smoking abstinence or nicotine reduction will be assessed by measuring smoking status (cigarettes smoked per day) and nicotine dependence will be assessed using the Fagerström test [19]. Nicotine abstinence will be additionally confirmed by using the NicAlert cotinine saliva test. Quality of life will be assessed with the German version of the 36-Item Short Form Survey (SF-36; index values range from 0 to 1, with higher scores indicating better quality of life) including covering physical functioning, bodily pain, role limitations due to physical health problems, role limitations due to personal or emotional problems, emotional well-being, social functioning, energy/fatigue, and general health perceptions during the past 4 weeks [20]. Mental health will be assessed using the Hospital anxiety and depression scale (HADS) [21].

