### Plans for collection, laboratory evaluation and storage of biological specimens for genetic or molecular analysis in this trial/future use {33}

Nicotine abstinence will be confirmed by using the NicAlert saliva test. The test will be performed by an advanced nurse practitioner during a routine hospital visit of the participant. The NicAlert saliva test is a point of contact test detecting six ranges of cotinine concentrations from 0 to 2000+ ng/ml. The only data collected is the category of concentration. No biological samples will be stored, and no further laboratory tests will be carried out. The test kit and the saliva sample will be immediately destroyed after use.

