The Fagerström test results, the quality of life (SF-36 Index) and the smoking status (cigarettes smoked per days) will be measured repeatedly over time from baseline, and for each outcome, mixed-effects models will be used to estimate the treatment effect and also to quantify the time*treatment interaction. The result of NicAlert Saliva test between treatment groups will be evaluated by applying chi-square test.

Cost-effectiveness analyses will be performed from a health care institution as well as a population public health perspective. First, hospital costs in both arms with and without costs of the tobacco treatment specialist (TTS) consultation per session, and nicotine replacement products will be compared as averages per patient across treatment groups. Second, the incremental cost per additional quit and incremental cost per additional life year saved of the preoperative institutional smoking cessation program compared to usual care will be calculated. Utilities will be calculated based on quality-of-life measurements using the SF-36 questionnaire.

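### Saliva cotinine cannot confirm smoking abstinence while patients use the nicotine patches supplied to one arm only, so a between-arm comparison of tests taken in that period is biased against the intervention

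*Protocol article*

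**What the plan says.** All references are to the protocol article.

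- **Role of the test.** Outcomes {12} lists smoking abstinence or nicotine reduction as a secondary endpoint, assessed by cigarettes per day, and adds: "Nicotine abstinence will be additionally confirmed by using the NicAlert cotinine saliva test".
- **What the test measures.** The biological specimens item {33} states: "The NicAlert saliva test is a point of contact test detecting six ranges of cotinine concentrations from 0 to 2000+ ng/ml". It continues "The only data collected is the category of concentration" and "No biological samples will be stored, and no further laboratory tests will be carried out". Cotinine is therefore the only biochemical marker. The timing is given only as a routine hospital visit; Fig. 1, the participant timeline, is not available here.
- **Planned comparison.** Statistical methods {20a} states: "The result of NicAlert Saliva test between treatment groups will be evaluated by applying chi-square test". The text gives no rule for patients on nicotine replacement.
- **Intervention arm.** Intervention description {11a} states: "Patients will be encouraged by a TSS to use nicotine replacement with patches/gums/pills at their own discretion". Patients smoking 20 or more cigarettes a day get "a 4-week supply of 21mg/day, 2-week supply of 14 mg/day and a 2-week supply of 7 mg/days patches will be provided"; those smoking 10 to 20 "will receive a 4-week supply of 14 mg/day and a 4-week supply of 7 mg/day"; lighter smokers get patches for 4 to 8 weeks.
- **Control arm.** Under the choice of comparators {6b}, controls receive no study-specific cessation treatment, but may obtain cessation aids themselves.

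**The concern.** Cotinine is a breakdown product of nicotine, whether the nicotine comes from tobacco, a patch or gum. During patch use, the test cannot tell a quitter from a smoker. The trial supplies patches by randomised arm, so the resulting misclassification differs between arms: it removes true quitters mainly from the intervention count. A larger sample or another test statistic does not correct this.

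At stake is the biochemical check on whether the programme leads patients to stop smoking. A real effect could look smaller than it is, vanish, or in the extreme change sign.

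**Working it through.** **1. The plan's own figure.** The article gives no power for the cotinine comparison. Its only sample size is for the CCI: difference 13 − 5.5 = 7.5, SD 20, two-sided 5%, power 80%. A two-sample t-test needs 112.6, so 113 per arm and 226 in total, as stated. Allowing for dropout, 226 / 0.90 = 251.1, against 251 stated. The figure of 113 per arm is used below.

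**2. When supplied patches overlap with testing.** The first meeting is 4 weeks before surgery and the quit day 2 to 3 weeks before. End of supply, in weeks after surgery = length of supply − weeks before surgery at which it starts.

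| Patch start | 8-week supply ends | 4-week supply ends |
|---|---|---|
| 4 weeks before surgery | 8 − 4 = 4 weeks after | 4 − 4 = day of surgery |
| 3 weeks before | 8 − 3 = 5 weeks after | 4 − 3 = 1 week after |
| 2 weeks before | 8 − 2 = 6 weeks after | 4 − 2 = 2 weeks after |

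With an 8-week supply, a test at admission or in the first 4 to 6 weeks after surgery can fall inside the patch period. A test at 90 days (about 13 weeks) or 12 months falls outside it, unless patients start later or continue with their own products.

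**3. Effect on the observed rates.** Let q be the true abstinence rate in an arm and u the share of its quitters on nicotine replacement when tested. Treat the test as negative or positive, and count every quitter on nicotine replacement as positive. Then:

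observed negative rate = q × (1 − u)

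The documents give neither q nor u, so all values are assumptions. Power is the two-sided 5% normal approximation for two proportions with 113 per arm. True abstinence is set at 30% versus 10%.

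| u, intervention | u, control | Observed rates | Difference (points) | Power |
|---|---|---|---|---|
| 0 | 0 | 30% vs 10% | +20 | 97% |
| 25% | 0 | 22.5% vs 10% | +12.5 | 72% |
| 50% | 0 | 15% vs 10% | +5 | 20% |
| 75% | 0 | 7.5% vs 10% | −2.5 | sign reversed |
| 25% | 10% | 22.5% vs 9% | +13.5 | 80% |
| 50% | 10% | 15% vs 9% | +6 | 28% |
| 50% | 50% | 15% vs 5% | +10 | 71% |

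Example, third row: 0.30 × (1 − 0.50) = 0.15 and 0.10 × (1 − 0) = 0.10.

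With no control use, the apparent effect vanishes at u = 1 − 10/30 = 67%. Under other assumed rates the point differs: 1 − 10/40 = 75% for 40% versus 10%, and 1 − 20/30 = 33% for 30% versus 20%.

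The last row shows what equal use does. The ratio of the rates stays at 3, as in truth, but the difference is still halved.

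**The case against.** The strongest objection is that the bias depends on test times that cannot be seen here. NicAlert appears in the caption of Fig. 1, so the schedule may be fixed there, and secondary endpoints run to 12 months. If the comparison uses only late visits, little bias remains. This stands, and it is why the point is limited to tests taken during nicotine-replacement use. A reader might infer that the abstinence comparison as a whole is biased; the documents do not support that.

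Three further inferences are tempting and also go too far:

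- **That nicotine-replacement use goes unrecorded.** The sentence on keeping only the concentration category describes what is retained from the saliva sample. The cost comparison in {20a} includes nicotine replacement products, so some data on them are needed. What can be said is that the article states no link between use and test result.
- **That the trial has no sound measure of abstinence.** Cigarettes per day is reported separately, has its own mixed-effects model, and is not affected by patches.
- **That the cost per additional quit is wrong.** The article does not say which measure defines a quit. The error carries over only if the cotinine-verified count is used.

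Two more objections concern size and place. Control patients may use their own nicotine replacement, which softens the bias, and the article states no cut-off for the six ranges, so the binary reading above is an assumption. The statistical analysis plan, Additional file 3, is not shown and may contain a rule for users. That possibility does not alter what the article itself states: this marker, compared between arms by this test, with patches supplied to one arm.

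**Conclusion.** The concern holds in a limited form. For any NicAlert test taken during nicotine-replacement use, the stated comparison measures nicotine exposure rather than smoking, and it is biased against the intervention as long as use among quitters is more common in that arm. For supplied patches this covers tests up to about 4 to 6 weeks after surgery. Results at 90 days or 12 months should be little affected unless use continues.

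The direction follows from the design; the size does not. The fall in power from 97% to about 72% or 20% rests on assumed abstinence of 30% versus 10%, 25% or 50% of intervention quitters on nicotine replacement, no control use, 113 patients per arm and a negative/positive reading of the test.

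This affects a secondary endpoint. The primary CCI analysis and its sample size are untouched. The point is worth correcting because use at the time of a test cannot be reliably recovered later, but it does not threaten the trial's main conclusion.

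**What to change.** 1. Record current nicotine-replacement use with every NicAlert test.
2. Base the between-arm cotinine comparison on a named visit after the supplied patches have ended. Label earlier results as nicotine exposure, not smoking abstinence.
3. At earlier visits, use self-reported smoking as the abstinence measure. Add two sensitivity analyses: nicotine-replacement users counted first as abstinent, then as smokers.
4. State which measure defines a quit in the cost per additional quit.

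Replacing the chi-square test by a regression model would not help, because the problem lies in the classification.

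The cost is one question at a visit that already takes place, plus wording in the analysis plan. The drawback is that abstinence during nicotine-replacement use then rests on self-report, mainly in the intervention arm. Counting such patients as abstinent waives biochemical proof chiefly where it favours the intervention, so both sensitivity analyses should be reported.

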Morbidity may influence the endpoints, therefore Charlson Comorbidity Index [22] and the American Society of Anaesthesiologists (ASA) physical status classification [23] will be assessed for each patient at baseline. The following characteristics measured at baseline are further described: age, gender, surgical procedure, underlying medical conditions and the stage of the Transtheoretical Model (TTM) of behaviour change.

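### The NicAlert abstinence result gets an unadjusted chi-square with no effect estimate, although prognostic baseline data are collected: a modest loss of precision, not a bias

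*Protocol article*

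**What the plan says.** All places are in the protocol article.

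- **Test for the saliva result.** Statistical methods {20a}: "The result of NicAlert Saliva test between treatment groups will be evaluated by applying chi-square test". No covariate and no effect measure is named.
- **Role of the saliva test.** Outcomes {12} lists abstinence or nicotine reduction among several secondary endpoints, assessed through cigarettes per day. It adds: "Nicotine abstinence will be additionally confirmed by using the NicAlert cotinine saliva test". The section on biological specimens {33} describes the test as "detecting six ranges of cotinine concentrations from 0 to 2000+ ng/ml", with only the category recorded.
- **Baseline predictors.** Outcomes {12} lists "surgical procedure, underlying medical conditions and the stage of the Transtheoretical Model (TTM) of behaviour change" among the characteristics to be described at baseline. According to {20a}, the Fagerström score, SF-36 index and cigarettes per day "will be measured repeatedly over time from baseline, and for each outcome, mixed-effects models will be used to estimate the treatment effect".
- **Other secondary outcomes.** {20a} says that "linear, logistic, or Poisson regression models including the randomized treatment group as an independent variable, will be used". Treatment group is the only term named.
- **Primary model.** {20a} adjusts the CCI for both minimisation variables and asks for a between-group difference with 95% confidence interval and p-value.
- **Balancing.** Sequence generation {16a} balances age and procedure risk, chosen as risk factors for complications. Readiness to quit and dependence are not balanced.

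**The concern.** Readiness to quit and nicotine dependence describe a patient's propensity to stop smoking more directly than age or procedure risk do. The plan collects both but uses neither in the comparison of confirmed abstinence. The planned method also sits apart from its surroundings: the primary model is adjusted and yields an interval, other secondary outcomes get regression models, and the saliva result gets only a test.

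Two things are at stake. The first is precision, in a trial sized for the CCI and not for abstinence. The second is a usable result. The same section plans a cost per additional quit, which needs a difference in quit rates and its uncertainty; a chi-square p-value supplies neither.

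**Working it through.** **1. The plan's own figure.** Sample size {14} gives CCI means of 13 and 5.5 (difference 7.5), SD 20, two-sided 5% and 80% power.

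- Normal formula: 2 × (1.96 + 0.84)² × 20² / 7.5² = 111.5, so 112 per arm.
- The t-test version gives 112.6, so 113 per arm and 226 in total, as stated.
- 226 / 0.9 = 251.1, stated as 251.

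Both figures reproduce. They concern the CCI only; no power for abstinence is given.

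**2. Chi-square power for abstinence, 113 per arm.** The protocol gives no quit rates, so these are assumptions: 10% vs 20%, 56%; 20% vs 35%, 72%; 10% vs 25%, 85%.

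**3. Gain from adjustment (simulation, 226 patients).**

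Set A: 3,000 trials per scenario, chi-square against a logistic model with two standardised covariates (stage, dependence). The assumed odds ratio (OR) per SD is the same for both.

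| Assumed rates | OR 1.3 | OR 1.5 | OR 2.0 |
|---|---|---|---|
| 10% vs 20% | 57→57% | 58→59% | 56→61% |
| 10% vs 25% | 86→87% | 86→87% | 86→89% |
| 20% vs 35% | 71→73% | 72→75% | 71→77% |

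Set B: 1,500 trials per scenario, logistic model without and with covariates. Assumed control quit rates are 8%, 20% and 40% in three stages holding 30%, 40% and 30% of patients, with a dependence effect of 0 to −0.7 log-odds per SD.

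- True OR 2.0: 55.7→60.7%, 53.9→59.0%, 50.6→58.5%.
- True OR 2.5: 80.5→83.1%, 79.9→83.7%, 75.3→82.4%.

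Set A gains about 0 to 6 points, Set B 2.6 to 7.9. Set B is higher because its stage effect is strong throughout. The log-odds are −2.44, −1.39 and −0.41, with a weighted SD of about 0.79, so the OR per SD is e^0.79 ≈ 2.2.

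At the upper end of Set A, moving from 71% to 77% power corresponds to (1.96 + 0.739)² / (1.96 + 0.553)² ≈ 1.15, or roughly 34 extra patients on 226.

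**4. Validity.** With no treatment effect (Set A), type I error was 4.5–5.6% for the chi-square and 4.6–5.9% for the adjusted model. About 13% of trials had a stage imbalance above 0.2 SD; among these, chi-square false positives were 4–7%.

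**5. Size of a chance imbalance (Set B inputs).**

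- SD of the between-arm difference in the share of the readiest stage: √(2 × 0.3 × 0.7 / 113) = 0.061.
- A surplus there displaces patients from both other stages, whose average quit rate is (0.3 × 8% + 0.4 × 20%) / 0.7 = 14.9%. The relevant gap is 40 − 14.9 = 25.1 points.
- A one-SD imbalance shifts the quit-rate difference by 0.061 × 25.1 ≈ 1.5 points.
- At a true OR of 2.0 the overall rates are 22.4% and 34.9%, and the standard error of the difference is √[(0.224 × 0.776 + 0.349 × 0.651) / 113] ≈ 6 points. The shift is about a quarter of that.

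**6. Unadjusted odds ratio.** With perfectly balanced arms, those rates give (0.349 / 0.651) / (0.224 / 0.776) ≈ 1.86, although the OR within each stage is 2.0. The marginal and conditional odds ratios are different quantities.

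**7. Model size.** Stage in three levels (2) + Fagerström (1) + minimisation factors (2) = 5 covariate degrees of freedom. Expected quitters are 113 × (0.224 + 0.349) ≈ 65 on Set B inputs at OR 2.0, and 113 × (0.10 + 0.20) ≈ 34 at 10% vs 20%.

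**Limits.** Neither set includes the minimisation factors, missing saliva tests or a chi-square on all six categories.

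**The case against.** The strongest reply is that nothing here is wrong. A chi-square test between randomised arms is valid, adjustment of a secondary endpoint is a matter of preference, and the SAP, which is not shown, may already settle it. The regression sentence in {20a} says that the models include treatment group, which does not rule out further terms. The gain in power rests on assumed rates and is often negligible.

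Most of this stands. It limits the point to efficiency and reporting. It does not remove it, because the protocol names the test for this result. If the SAP adjusts, the two documents need to be aligned; if it does not, the improvement is available at almost no cost.

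A reader might infer more than the protocol supports:

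- *That chance imbalance in motivation biases the result and would pass for a programme effect.* Such imbalance is already within the test's error rate (steps 4 and 5). It costs precision.
- *That a smaller unadjusted odds ratio means lost effect.* It reflects non-collapsibility (step 6); a marginal risk difference is not attenuated in this way.
- *That abstinence as a whole, or the main public-health result, rests on this test.* The sentence covers only the saliva result. Cigarettes per day has a mixed model from baseline. The Background {6a} links abstinence to a public-health perspective, but Outcomes {12} lists it as one secondary endpoint among several.

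**Conclusion.** The point holds as a modest efficiency and reporting improvement. The protocol commits the saliva result to a test that ignores collected prognostic information and gives no effect estimate. On the assumed quit rates and covariate strengths, the cost is about 0 to 8 points of power with 226 patients, and 3 points or less unless the covariates are strongly prognostic. Type I error is about 5% with either method, so no bias is being corrected. The missing effect estimate does not depend on these assumptions: the sentence names none, and the planned cost per additional quit needs one.

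**What to change.** In Statistical methods {20a}, replace the chi-square sentence by a logistic regression of NicAlert-confirmed abstinence (yes/no) on treatment group, the two minimisation factors, baseline stage of change (sparse stages merged by a rule fixed in advance) and baseline Fagerström score. Report the adjusted odds ratio and the standardised risk difference, each with a 95% confidence interval, and use the risk difference for the cost per additional quit. The model needs the six categories reduced to yes/no; if the SAP already defines the cut-off and time point, refer to it.

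The cost is a wording change in the protocol and, if needed, the SAP, with no new data. The model spends at least 5 covariate degrees of freedom, which is why stages should be merged if quitters are few (about 34 at 10% vs 20%). Make the change before abstinence is compared by arm. The cigarettes-per-day model needs no change.
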